### Sample Size

The sample size is calculated based on the primary outcome (ie, OKS), by considering 80% power (*P*=.05) with a 15% difference in the control group and the intervention group. The standard deviation within each group in the TKR trials can vary based on factors such as number of trial sites (eg, single-center vs multicenter) and heath care cover (eg, public patients vs private patients). Furthermore, in a repeated measure scenario or when considering multiple assessments within a trial (eg, baseline, prehabilitation, 12 weeks rehabilitation, 12 months free living), the correlation among repeated measures needs to be considered as well. Based on these factors the sample size is presented in Table 2 for a variety of scenarios. A low subject variation can be expected with participants when considering only 1 trial site or 1 type of health care cover (eg, public), and a high variation can be expected when participants are mixed. A high correlation in repeated measures can be expected for patients with big differences in the outcome measure within the assessment points.

**Table 2 table2:** Estimated sample size (with 20% loss) based on standard deviation (SD) within groups and correlation among baseline and 3 repeated measures [80% power, *P*=.05, 15% difference].

SD within group/ correlation repeated measure	Low repeated correlation (SD 0.2)	Mid repeated correlation (SD 0.5)	High repeated correlation (SD 0.8)
Low subject variation (SD 0.2)	31	46	60
Mid subject variation (SD 0.5)	170	262	360
High subject variation (SD 0.8)	432	674	914

We estimate that a total of 262 patient participants would be sufficient for this study; however, we expect a maximum of 320 participants from the 5 trial sites based on their rate of TKR surgeries during the trial timeline. A minimum sample size of 100 is suggested for using OKS as the primary outcome measure [33]. Based on the literature [1,7,34], 80% power (*P*=.05) with a 15% difference in the control group and the intervention group has been reported for primary outcome measure.

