### Statistical Analysis

Statistical data analysis will be performed using an intention-to-treat approach. Mixed model analysis will be used for continuous variables (primary and secondary outcomes) measured at week 0, week 12, and week 52 for those receiving the TKR platform compared with usual care by time effects. Fixed effects will be included for the intervention, the time points, and the interaction between the 2 variables. These models will also account for relevant covariates such as baseline (4 weeks before surgery) measures, participant sex, baseline levels of motivation, etc. These covariates will be entered as fixed effects. Due to potential confounding effects between different hospitals, these will be also assessed in the mixed model as random effects. Sensitivity analysis will be used to assess the impact of these covariates before the final model is constructed. Other outcome measures of app usage, self-management (eg, physical activity), and compliance with the program (eg, physiotherapy exercise) will be analyzed using logistic or conditional logistic regression to adjust the comparisons for other variables for categorical or ordinal variables and multiple regression for continuous variables. All statistical analysis will be done using Excel (Microsoft Corp), R (R Foundation), or SPSS (IBM Corp).

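### The 80% power at 262 patients belongs to a test on the mean of four OKS readings including baseline, not to the planned baseline-adjusted analysis of weeks 0, 12 and 52

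*Protocol article*

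**What the plan says.** In the protocol article, the Sample Size section bases the calculation on the OKS, with "80% power (*P*=.05) with a 15% difference in the control group and the intervention group". Table 2 is captioned "Estimated sample size (with 20% loss) based on standard deviation (SD) within groups and correlation among baseline and 3 repeated measures". It crosses three within-group SDs (0.2, 0.5, 0.8) with three correlations (0.2, 0.5, 0.8). The column heads give the correlations as SDs; the middle one begins "Mid repeated correlation (SD 0.5". In the SD 0.5 row the sizes are 170, 262 and 360. The text adopts the middle cell, 262, as sufficient and expects at most 320 patients from the five sites.

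The Statistical Analysis section states: "Mixed model analysis will be used for continuous variables (primary and secondary outcomes) measured at week 0, week 12, and week 52". The model has fixed effects for intervention, time and their interaction. The measure taken 4 weeks before surgery enters as a covariate, not as an outcome. Under Overview and Aims, the active intervention begins at about that same point, when surgery is scheduled.

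**The concern.** The two sections use the baseline reading in incompatible ways. Table 2 counts it as one of four outcome readings that carry the treatment difference. The analysis uses it to remove between-patient variation from the later readings. At baseline, randomised groups can differ only by chance, so a 15% difference there is not a possible treatment effect.

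The roles also have opposite consequences. When readings are averaged as outcomes, high correlation means that each extra reading adds little, so the required size rises. When one reading is a covariate, high correlation means that it explains more of the outcome, so the required size tends to fall. A table built on the first role cannot give the power of an analysis built on the second, nor show how sensitive that analysis is to the correlation. The cell taken from it is the main calculation behind calling 262 sufficient.

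**Working it through.** **Inputs (Sample Size and Table 2; allocation from Overview and Aims).** Difference δ = 0.15; SD σ = 0.5, so δ/σ = 0.30; correlation ρ = 0.5; power 80%; α = 0.05, taken as two-sided because one-sided does not reproduce the table; 1:1 allocation; 20% loss. All readings are taken as equally correlated.

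**Step 1: reproduce Table 2.** For the mean of m equally correlated readings, the variance factor is f = (1 + (m − 1)ρ)/m, and

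n per arm = 2(1.96 + 0.8416)² σ² f / δ².

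With m = 4 and ρ = 0.5, f = 0.625 and n = 2 × 7.849 × 0.25 × 0.625 / 0.0225 = 109.0. The total is 218, and 218 × 1.2 = 261.6, that is 262.

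For the other eight cells, exact-test totals of 26, 38, 50, 142, 300, 360, 562 and 762, multiplied by 1.2 and rounded, give 31, 46, 60, 170, 360, 432, 674 and 914. All eight match. In the chosen cell the exact test gives 220 × 1.2 = 264, two more than printed; the normal approximation gives 262.

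Three readings without baseline do not fit (middle cell 236 × 1.2 = 283). A baseline-adjusted single visit happens to need 262 at ρ = 0.5 before any loss, but it needs 336 and 126 at ρ = 0.2 and 0.8, where the table has 170 and 360 including loss.

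**Step 2: variance factors for the planned analysis.** For the mean of k follow-up visits adjusted for baseline, f = (1 + (k − 1)ρ)/k − ρ².

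| Test | ρ = 0.2 | ρ = 0.5 | ρ = 0.8 |
|---|---|---|---|
| Table 2: mean of four, baseline included | 0.40 | 0.625 | 0.85 |
| Baseline-adjusted mean of three visits | 0.43 | 0.42 | 0.23 |
| Baseline-adjusted single visit | 0.96 | 0.75 | 0.36 |

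For the mean of two visits at ρ = 0.5, f = 0.75 − 0.25 = 0.50.

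**Step 3: power at the planned sizes.** 262 × 0.8 = 209.6, about 105 completers per arm; 320 × 0.8 = 256, or 128 per arm. Power = Φ[(δ/σ)√(n/2)/√f − 1.96]. Here 0.30 × √52.5 = 2.174 and 0.30 × √64 = 2.400. For example, a single visit at 262 gives 2.174/0.866 − 1.96 = 0.55, or 71%.

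| Baseline-adjusted contrast, SD 0.5, ρ 0.5 | f | Difference | 262 enrolled | 320 enrolled |
|---|---|---|---|---|
| Mean of weeks 0, 12, 52, common effect | 0.417 | 0.15 | 92% | 96% |
| Mean of weeks 12 and 52 | 0.50 | 0.15 | 87% | 92% |
| Single visit | 0.75 | 0.15 | 71% | 79% |
| Mean of weeks 0, 12, 52, effect only after surgery | 0.417 | 0.15 × 2/3 = 0.10 | 61% | 70% |

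**Step 4: sizes needed for 80% power at SD 0.5, ρ 0.5.** Total N = 4 × 7.849 × 0.25 × f / 0.0225, divided by 0.8 for loss. The three-visit mean needs 145.4/0.8 = 182. A single visit needs 261.6/0.8 = 327. The table's ×1.2 falls slightly short of a 20% loss allowance: 262 leaves about 210 completers, not the 218 its own calculation calls for.

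**The case against.** The strongest reply is that the trial may be well powered. For an effect common to all three visits, 262 gives about 92%, and 87% for the mean of weeks 12 and 52, so for these contrasts the table is conservative. At 320 even a single visit reaches 79%. This stands. A reader might infer that the trial is underpowered throughout, but the documents do not support that.

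Three other stronger readings are tempting and also fail:

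- Applying Table 2's four-reading test with no effect at baseline (difference 0.75 × 0.15 = 0.1125) gives 54% at 105 per arm. With an effect only after surgery (0.075) it gives 28%. These show that the table's effect assumption is untenable. They are not the trial's power, because the plan does not run that test.
- It is too strong to say that the correlation gradient is simply reversed. That is clear for a single visit. For the three-visit mean the factor is nearly flat from 0.2 to 0.5 and then falls. Table 2's rise is correct for its own test.
- Week 12 cannot be taken as the intended primary contrast, because the article names no single visit as primary. The effect-only-after-surgery case is likewise an assumption: the intervention starts about 4 weeks earlier and week 0 is an analysed outcome.

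The article does not print its formula, so the four-reading mean is inferred. The caption names those four readings, however, and no other variant tried reproduces the table. The SD labels on the correlation columns are a slip whose meaning can be recovered.

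**Conclusion.** The point holds as a mismatch between the sample-size model and the analysis model, not as an arithmetic error inside Table 2. The 80% at 262 describes a test that includes the pre-treatment reading as an outcome, and the planned analysis does not use that test. On the plan's own middle inputs, the planned model's power at 262 lies between 61% and 92% across the contrasts examined. Which value applies depends on a contrast that the article does not identify. Table 2 should also not be used to judge sensitivity to correlation in the planned model.

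These figures rest on equal correlation between all readings, the 15% difference and the SDs lying on one scale as in Table 2, two-sided testing, no allowance for site effects, and 20% loss with completers analysed.

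**What to change.** - Identify the primary OKS contrast within the planned mixed model. The sponsor should choose it; this review does not prescribe a visit.
- Recompute Table 2 for that contrast with the baseline-adjusted factor: (1 + 2ρ)/3 − ρ² for the three-visit mean, or 1 − ρ² for a single visit. State at which visits the 15% difference is assumed.
- Allow for loss by dividing by 0.8.
- Restate the power at 262 and at 320.
- Relabel the column heads as correlations.

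The cost is one recalculated table and a few sentences, with no new data. The only drawback is that the stated power becomes less favourable if a single visit is chosen: about 71% at 262 and 79% at 320, with 327 needed for 80%.

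### The 20% loss allowance in Table 2 appears to multiply by 1.2 rather than divide by 0.8, so 262 enrolled leaves about 210 completers where 218 to 220 are needed

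*Protocol article*

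**What the plan says.** The Sample Size section of the protocol article bases the calculation on the Oxford Knee Score, "by considering 80% power (*P*=.05) with a 15% difference in the control group and the intervention group". Table 2 is titled "Estimated sample size (with 20% loss") and covers three within-group standard deviations crossed with three values of the "correlation among baseline and 3 repeated measures". Its entries, by row, are 31, 46, 60; 170, 262, 360; 432, 674, 914.

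The text then adopts the cell where the row "Mid subject variation (SD 0.5") meets the column "Mid repeated correlation (SD 0.5"): "We estimate that a total of 262 patient participants would be sufficient for this study". It adds that up to 320 are expected from the five sites. The Methods part of the abstract gives 320 as the trial size. Neither the sample size formula nor the way the 20% was applied is stated.

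**The concern.** If n patients must complete and a fraction 0.20 is lost, n/(1 − 0.20) must be enrolled. Multiplying n by 1.2 looks similar but falls short, because 1.2 × 0.8 = 0.96: after the stated loss only 96% of the required patients remain. The Table 2 entries look like products of 1.2. If they are, every scenario in the table misses its own 80% power at its own 20% loss, including the 262 on which the trial relies. The practical risk is that recruitment is closed at 262 because the protocol calls that number sufficient.

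**Working it through.** **Inputs (all from the Sample Size section unless noted)**

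- Power 80%, significance level 0.05. Sidedness is not stated, so two-sided is assumed.
- Difference 15%, used as 0.15 on the same scale as the table's standard deviations. This is an assumption; it is the scale that reproduces Table 2.
- Adopted cell: standard deviation σ = 0.5 and correlation ρ = 0.5. The column head labels the correlation as an SD.
- Number of measures m = 4 (baseline plus three).
- Allocation 1:1 (Methods, Overview and Aims).
- Loss 20%.

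**Step 1. Required completers in the adopted cell**

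For a two-group comparison of the mean of m measures, the total is

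N = 4 (z₀.₉₇₅ + z₀.₈₀)² (σ/0.15)² × [1 + (m − 1)ρ]/m

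With (1.960 + 0.842)² = 7.849, (0.5/0.15)² = 11.11 and [1 + 3 × 0.5]/4 = 0.625:

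N = 4 × 7.849 × 11.11 × 0.625 = 218.0

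With equal arms, or with the noncentral F distribution on N − 2 degrees of freedom, the smallest even total reaching 80% is 220. F power at 218 is 79.6%.

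**Step 2. Reproduce Table 2**

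The same model was applied to all nine cells (noncentral F, equal arms), with loss allowed for in both ways.

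| σ | ρ | Completers | × 1.2 | Table 2 | ÷ 0.8 |
|---|---|---|---|---|---|
| 0.2 | 0.2 | 26 | 31.2 | 31 | 32.5 |
| 0.2 | 0.5 | 38 | 45.6 | 46 | 47.5 |
| 0.2 | 0.8 | 50 | 60.0 | 60 | 62.5 |
| 0.5 | 0.2 | 142 | 170.4 | 170 | 177.5 |
| 0.5 | 0.5 | 220 | 264.0 | 262 | 275.0 |
| 0.5 | 0.8 | 300 | 360.0 | 360 | 375.0 |
| 0.8 | 0.2 | 360 | 432.0 | 432 | 450.0 |
| 0.8 | 0.5 | 562 | 674.4 | 674 | 702.5 |
| 0.8 | 0.8 | 762 | 914.4 | 914 | 952.5 |

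Multiplication by 1.2 gives eight of the nine printed values after rounding. The ninth, 262, is what 218 gives: 218 × 1.2 = 261.6. Division by 0.8 gives none of the nine, and in the last cell it differs from the printed figure by 38.5.

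Other models were tried for the 262 cell. A one-sided ANCOVA with division by 0.8 gives 260, and a two-sided ANCOVA with no loss gives 262. Both are ruled out by the rest of the table: under ANCOVA the sample size falls as correlation rises, whereas Table 2 rises.

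**Step 3. What 262 delivers**

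- Completers after 20% loss: 262 × 0.8 = 209.6, against 218 to 220 needed.
- Power at about 210 completers: 78.1% (noncentral F) or 78.5% (normal approximation).
- Loss that 262 can absorb: 1 − 218/262 = 16.8%, or 1 − 220/262 = 16.0%.

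**Step 4. Corrected enrolment**

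- 218/0.8 = 272.5, so 273 (274 with equal arms).
- 220/0.8 = 275 (276 with equal arms).
- Shortfall: 273 − 262 = 11 to 275 − 262 = 13 patients.

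**The case against.** There are four fair points on the other side.

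1. **The multiplier is inferred.** The article prints no formula, and no single rule tried gives all nine cells exactly: the noncentral F gives 264 in the adopted cell, while the normal approximation gives 262 there but misses elsewhere (for example 139.5 × 1.2 = 167.4 against 170). This stands as a caveat and explains why the corrected target is a range. It does not rescue the table, since division by 0.8 fits no cell under the same model.

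2. **78% is a complete-case figure.** The Statistical Analysis section plans an intention-to-treat mixed model, which uses partial data. Under the table's own model, a patient with two of four measures carries (2/1.5)/(4/2.5) = 0.83 of the information. If all 52.4 lost patients left after week 0, the effective total would be 209.6 + 52.4 × 0.83 ≈ 253, with power about 85%. If they left after week 12, it would be about 259, with power about 86%. This is fair but optimistic: it credits baseline and week 0 with the full treatment effect, and the article does not say when losses are expected. It also does not alter the fact that the authors chose to allow for 20% loss, and the allowance is miscalculated.

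3. **The trial expects 320.** At 320, 320 × 0.8 = 256 complete and power is about 86%, so nothing is lost. But 320 is described as a maximum, and the Timelines section makes the study's duration subject to recruitment. The figure called sufficient is 262.

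4. **The change is small beside the table's own spread**, where the cells around the adopted one run from 46 to 674. This is true and limits the priority of the point.

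**Conclusion.** The concern holds. The Table 2 entries are best explained as required completers multiplied by 1.2, which does not cover a 20% loss. For the adopted cell, 262 should read 273 to 275, about 4 to 5% more. As printed, 262 gives about 78% power at 20% loss.

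This rests on the reconstructed model (mean of four measures, difference 0.15 on the scale of the SDs, two-sided 0.05, 1:1) and on lost patients contributing nothing, as a conventional loss allowance assumes. The consequence is modest: about 2 points of power at worst, and none if enrolment reaches the corrected figure. It is a wrong number that the trial relies on and should be corrected, but it does not threaten the design.

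**What to change.** Recompute Table 2 by dividing the required completers by 0.8. By row this gives 33, 48, 63; 178, 275, 375; 450, 703, 953. Restate the target as 275 (276 if the arms are to be equal), and add one line giving the formula and how loss was applied.

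Alternatively, keep 262 and state that it gives about 78% power with 20% loss, or that it maintains 80% power only up to 16 to 17% loss.

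Either way the cost is one table and one sentence. No enrolment beyond the 320 already expected is needed.

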### Statistical Analysis

Statistical data analysis will be performed using an intention-to-treat approach. Mixed model analysis will be used for continuous variables (primary and secondary outcomes) measured at week 0, week 12, and week 52 for those receiving the TKR platform compared with usual care by time effects. Fixed effects will be included for the intervention, the time points, and the interaction between the 2 variables. These models will also account for relevant covariates such as baseline (4 weeks before surgery) measures, participant sex, baseline levels of motivation, etc. These covariates will be entered as fixed effects. Due to potential confounding effects between different hospitals, these will be also assessed in the mixed model as random effects. Sensitivity analysis will be used to assess the impact of these covariates before the final model is constructed. Other outcome measures of app usage, self-management (eg, physical activity), and compliance with the program (eg, physiotherapy exercise) will be analyzed using logistic or conditional logistic regression to adjust the comparisons for other variables for categorical or ordinal variables and multiple regression for continuous variables. All statistical analysis will be done using Excel (Microsoft Corp), R (R Foundation), or SPSS (IBM Corp).

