**Methods:**

The study will evaluate the TKR platform through a randomized controlled trial conducted at multiple sites (N=5) in a number of states in Australia with 320 patients undergoing TKR surgery; the trial will run for 13 months for each patient. Participants will be randomized to either a control group or an intervention group, both receiving usual care as provided by their hospital. The intervention group will receive the app and wearable activity tracker. Participants will be assessed at 4 different time points: 4 weeks before surgery, immediately before surgery, 12 weeks after surgery, and 52 weeks after surgery. The primary outcome measure is the Oxford Knee Score. Secondary outcome measures include quality of life (Short-Form Health Survey); depression, anxiety, and stress (Depression, Anxiety, and Stress Scales); self-motivation; self-determination; self-efficacy; and the level of satisfaction with the knee surgery and care delivery. The study will also collect quantitative usage data related to all components (app, activity tracker, and Web portal) of the TKR platform and qualitative data on the perceptions of the platform as a tool for patients, carers, and clinicians. Finally, an economic evaluation of the impact of the platform will be conducted.

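### The mixed model gives baseline OKS one slope across a pre-operative and two post-operative visits; if baseline predicts these visits unequally, the treatment contrasts lose some precision, and a baseline-by-time term avoids this

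*Protocol article*

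**What the plan says.** The Statistical Analysis section of the protocol article describes one mixed model for continuous endpoints, primary and secondary alike, "measured at week 0, week 12, and week 52 for those receiving the TKR platform compared with usual care by time effects". The model terms are then listed: "Fixed effects will be included for the intervention, the time points, and the interaction between the 2 variables". Baseline comes in through the next sentence, which adjusts for "relevant covariates such as baseline (4 weeks before surgery) measures" together with sex, motivation and others. Of all of these it says: "These covariates will be entered as fixed effects". Hospital is the only random effect mentioned, and no within-patient covariance structure is named. On how final the model is, the section says: "Sensitivity analysis will be used to assess the impact of these covariates before the final model is constructed".

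The Abstract (Methods) places the four assessments at "4 weeks before surgery, immediately before surgery, 12 weeks after surgery, and 52 weeks after surgery". So of the three visits modelled as outcomes, week 0 precedes the operation and weeks 12 and 52 follow it.

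**The concern.** A covariate entered as a main effect has the same coefficient at every visit. Here that coefficient must serve two different situations. Baseline and week 0 are about four weeks apart and both describe the unoperated knee. Weeks 12 and 52 describe a knee that has been replaced. It is reasonable to expect baseline OKS to predict week 0 well and the later visits less well. If so, no single slope fits all three visits.

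What is at stake is precision, not validity. Baseline is measured before the intervention and allocation is random, so a wrong slope does not bias the treatment contrasts. It leaves residual variance that visit-specific slopes would remove, in a design where weeks 12 and 52 carry the information on recovery.

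**Working it through.** **The plan's own figure.** Table 2 gives 262 patients for SD 0.5, one correlation of 0.5 among baseline and three repeated measures, a difference of 0.15, 80% power and P=.05 (two-sided reproduces the table). Per arm: 2 x (1.96 + 0.84)^2 x 0.5^2 x [(1 + 3 x 0.5)/4] / 0.15^2 = 109.0. Both arms with 20% added: 109.0 x 2 x 1.2 = 261.6, so 262 is reproduced. The planning uses one common correlation and gives no visit-specific values.

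**Inputs for the check.** From the protocol: three outcome visits, SD 0.5, difference 0.15, N = 262 with 20% loss, so 262 x 0.8 / 2 = 105 completers per arm. Assumed, because the protocol does not give them: the correlation b_t of baseline with each visit, the correlations among the three visits, equal SDs, complete data, and the covariance structure.

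**Formulas** (variances in units of SD^2).
- With equal SDs the slope needed at visit t is b_t, and the residual variance with that slope is V_tt = 1 - b_t^2.
- The fitted common slope is a weighted mean of the b_t. With an unstructured covariance the weights are proportional to V^-1 1, where V is the residual covariance of the three visits given baseline. With a patient random intercept (or independent residuals) they are one third each.
- Variance of the visit-t contrast relative to visit-specific slopes: 1 + (b_t - common slope)^2 / V_tt.

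**Worked example.** Take b = 0.8/0.3/0.3 at weeks 0/12/52. Take between-visit correlations of 0.3 (week 0 with each later visit) and 0.6 (week 12 with week 52).
- V has diagonal 0.36, 0.91, 0.91 and off-diagonals 0.06, 0.06 and 0.51.
- The unstructured weights are 0.684, 0.158 and 0.158. Slope = 0.684 x 0.8 + 0.316 x 0.3 = 0.642.
- Week 12: 1 + (0.642 - 0.30)^2 / 0.91 = 1.129. Residual variance is 0.91 x 1.129 = 1.03, against 0.91 with visit-specific slopes.
- With SE = 0.5 x sqrt(variance x 2/105), week-12 power for a difference of 0.15 is about 57%, against about 63%.
- Random intercept: slope = (0.8 + 0.3 + 0.3)/3 = 0.467. Week 12: 1 + 0.167^2/0.91 = 1.031. Week 0: 1 + 0.333^2/0.36 = 1.309.

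**Range.** Entries are variance ratios against visit-specific slopes, in the order week 0 / 12 / 52.

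| b at weeks 0/12/52 | Between-visit correlations (0-12, 0-52, 12-52) | Unstructured: slope; ratios | Random intercept: slope; ratios |
|---|---|---|---|
| 0.5/0.5/0.5 | any | 0.50; 1.00 / 1.00 / 1.00 | 0.50; 1.00 / 1.00 / 1.00 |
| 0.6/0.4/0.4 | 0.3, 0.3, 0.6 | 0.50; 1.02 / 1.01 / 1.01 | 0.47; 1.03 / 1.005 / 1.005 |
| 0.7/0.3/0.3 | 0.3, 0.3, 0.6 | 0.54; 1.05 / 1.06 / 1.06 | 0.43; 1.14 / 1.02 / 1.02 |
| 0.8/0.4/0.3 | 0.4, 0.3, 0.6 | 0.65; 1.06 / 1.08 / 1.14 | 0.50; 1.25 / 1.01 / 1.04 |
| 0.8/0.3/0.3 | 0.3, 0.3, 0.6 | 0.64; 1.07 / 1.13 / 1.13 | 0.47; 1.31 / 1.03 / 1.03 |
| 0.8/0.3/0.3 | 0.4, 0.4, 0.6 | 0.67; 1.05 / 1.15 / 1.15 | 0.47; 1.31 / 1.03 / 1.03 |
| 0.85/0.2/0.2 | 0.3, 0.3, 0.6 | 0.73; 1.06 / 1.29 / 1.29 | 0.42; 1.68 / 1.05 / 1.05 |

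A simulation (109 per arm, 4,000 replicates) agrees with the formulas. For 0.8/0.4/0.3 it gave 1.07 and 1.12 at weeks 12 and 52 with an unstructured covariance, and 1.01 and 1.04 with a random intercept. As a yardstick, a variance ratio of 1.10 makes 262 patients worth 262/1.10 = 238.

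**The case against.** The other side has a good case. The document is a journal article, and baseline-by-visit terms and covariance structure are often left to an analysis plan. The text does not exclude a baseline-by-time term: its covariate list is illustrative, the fixed-effect wording mainly sets covariates apart from the random hospital effects, and the final model is left open. The only correlation assumption in the protocol, Table 2's single value, implies no loss at all. There is no bias, and no type I error problem is alleged.

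Most of this stands as a limit on the size of the point. It does not remove it. The section writes out the model's terms, names one interaction and gives baseline none. The sensitivity analysis it promises concerns the impact of the covariates and does not commit to a baseline-by-time term. A better specification is available at almost no cost.

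Four stronger readings are tempting, and the document does not support them:

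- A reader might infer that the pre-surgery visit dominates the adjustment. That needs an unstructured or similar covariance and a high correlation between baseline and week 0. The protocol states neither. With a random intercept each visit has weight one third.
- A reader might infer that the adjusted week-12 contrast is less precise than an unadjusted one. With an unstructured covariance this happens at 0.8/0.3 (1.03 against 1.00) or beyond. At 0.6/0.4 the variance is 0.85, at 0.7/0.3 it is 0.96-0.98, and at 0.8/0.4 it is 0.89-0.93, all better than unadjusted.
- A reader might extend the same size of loss to every scale. No calculation was made for the other outcomes, and the replaced-joint argument does not obviously carry over to mood or self-efficacy scores.
- A reader might want hospital handled the same way, as a fixed factor with hospital-by-time. The plan says: "Due to potential confounding effects between different hospitals, these will be also assessed in the mixed model as random effects". Nothing in the baseline-slope argument shows that choice to be wrong.

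**Conclusion.** The point holds as a conditional loss of precision and a cheap improvement, not as a demonstrated error. Read literally, the model ties one baseline slope to visits on both sides of the operation. If baseline predicts week 0 more strongly than the later visits, some contrasts carry avoidable variance whichever covariance is used. An unstructured fit puts more of it on weeks 12 and 52, and a random intercept puts more of it on week 0 (3% to 68% over the scenarios with unequal correlations).

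The size at week 12 runs from nothing, under Table 2's single correlation, to about 13-15% of variance at 0.8/0.3 with an unstructured covariance. More extreme correlations give more: 29% in the last row of the table, and higher still with other between-visit values. All visit-specific correlations, the between-visit correlations and the covariance structure are assumptions, so none of these figures is a prediction for this trial.

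**What to change.** State the fixed effects for OKS as intervention, time, intervention-by-time, baseline and baseline-by-time. Use the same form for the other continuous outcomes that Table 1 shows with a baseline measure (SF-36, DASS21, self-efficacy, range of motion). Fix the term in advance and do not let it depend on the covariate sensitivity analysis.

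The cost is one sentence of wording and two degrees of freedom per model (three visits, so two extra slopes), against about 210 completers (2 x 105). No new data are needed, the stated sample size is unchanged, and essentially nothing is lost if the correlations turn out equal. The handling of hospital need not change on account of this point.
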